The general approach for analyzing all the types of study outcomes separately (including the 3 primary end points and the secondary end points) will be the generalized linear mixed-effect models (GLMMs) for clustered measures, with the randomization block as the clustering variable. These models can handle a wide range of outcome types, including continuous, binary, ordinal, and count, and can account for the correlations among observations within the same cluster. Specifically, we will analyze each primary end point using a linear mixed-effect model, a special case of the GLMM. For secondary outcomes, we will use linear mixed-effect models to analyze mental well-being measures and readiness to change measures, mixed logit models to analyze the connection to services and support-related measures (binary: yes or no), mixed-effects quasi-Poisson regression models with the log link (a special case of GLMMs) for substance use frequency measures, and mixed-effects proportional odds ordinal logistic regression (another special case of GLMMs) for self-efficacy measures. The treatment effect on an outcome at 30 days will be assessed using a GLMM with the treatment allocation as the main explanatory variable and with adjustment for baseline outcome assessment value and other baseline prognostic factors as fixed effects and the randomization block as a random effect. By properly specifying the GLMM, a wide range of scientific hypotheses can be tested, including the primary ones regarding treatment effect estimation. The quality of statistical inferences will be substantiated through rigorous model checking and validation techniques. When statistical models assume that residuals at certain levels follow normal distributions, this assumption will be checked using a normal probability plot, in which the ranked residuals are plotted against corresponding points on a normal distribution curve. When substantial departures from the normal residual assumption are found, robust empirical SE estimates that are valid with nonnormal residuals will be used for statistical inference. We will use SAS software (version 9.4; SAS Institute Inc) and R (version 4.3.1; R Foundation for Statistical Computing) for the statistical analyses of our primary and secondary outcomes. Subgroup analysis will be performed using the GLMM on the subsets of data formed by the subgroup.

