Missing data will take two forms: (1) missed questions or items and (2) unit nonresponse or attrition (withdrawals and lost to follow-up). We anticipate that most missing data are owing to attrition, which leads to unit nonresponse at the 30-day assessment. To reduce bias and avoid the loss of statistical power in our analysis of primary and secondary outcomes, we will use likelihood-based direct estimation, which is equivalent to performing multiple imputations under the model to predict values for missing data. One advantage of using the abovementioned multilevel GLMMs for analyzing primary and secondary outcomes is that it uses all the available data by including those study units with missing outcome values and it produces valid inference under the assumption of missing at random, which is a more relaxed assumption of missing data mechanism than missing completely at random. The missing values will be regarded as missing at random when the nonresponse behavior is believed to be a function of observed data, particularly common when assessing mental health and substance use behaviors and using a digital self-report format. The potential bias of these inferences will be quantified if these missing data were suspected to be nonrandom even after conditioning on the observed data, using the methods [41,42] developed by our team member and implemented in R package *isni* [43]. In summary, state-of-the-art statistical methods will be used to address these missing data issues.

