### Continued Monitoring

There will be no stopping rules in this study—the anticipated benefits and unanticipated adverse effects are not life threatening and too small to merit such an approach. In addition, there will be no sequential analyses of the data: the analyses will commence at the end of the trial when the data manager provides the statistician with a blinded database for the analyses. Of note, data from the 2-week assessment completed by the intervention group will be removed from the data set used for the primary outcome analysis to maintain the blinding of the statistician.

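### The stated GLMM does not include participants with no 30-day outcome, so the claim that it retains them and avoids power loss is wrong, and the missing-at-random condition is narrower than the one stated

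*Protocol article*

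**What the plan says.** All of this is in the protocol article.

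- **Model (Statistical Analysis).** "The treatment effect on an outcome at 30 days will be assessed using a GLMM with the treatment allocation as the main explanatory variable", "with adjustment for baseline outcome assessment value and other baseline prognostic factors as fixed effects and the randomization block as a random effect". The models are for clustered measures "with the randomization block as the clustering variable". Each primary end point uses the linear mixed-effects version.
- **Joint test (Statistical Analysis).** A marginal multivariate model of PHQ-9, GAD-7 and USAUDIT-C comes first. The separate models follow if it rejects.
- **Missing data (Statistical Analysis).** "We anticipate that most missing data are owing to attrition, which leads to unit nonresponse at the 30-day assessment". Direct likelihood estimation is to reduce bias and avoid power loss, and is described as equivalent to multiple imputation under the model. An advantage claimed for the GLMMs is that "it uses all the available data by including those study units with missing outcome values". Values count as missing at random when nonresponse is believed to depend on observed data. Sensitivity to nonrandom missingness (the isni package) is examined "if these missing data were suspected to be nonrandom even after conditioning on the observed data".
- **2-week data.** Table 1 shows a 2-week assessment in the intervention arm only. Continued Monitoring adds that "data from the 2-week assessment completed by the intervention group will be removed from the data set used for the primary outcome analysis", to keep the statistician blinded.
- **Sample Size and Power.** 524 per arm are needed, raised to 748 per arm (1496 in total) for 30% attrition.

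**The concern.** Direct likelihood keeps a participant with a missing final outcome only when the model holds another response from that participant, such as a baseline or interim score modelled as an outcome with within-participant correlation. The stated model has none: baseline is a covariate, the 2-week scores are gone, and the random effect belongs to the block, not the person.

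Two things follow. Readers are told that nonresponders are included when they are not. The assumption for validity is also looser on paper than the model can support: 2-week symptoms and app use are observed, so dropout driven by them would meet the plan's description of missing at random, yet the primary model does not condition on them. If the claim stands, the matter looks settled, and the sensitivity analysis that should accompany a 30% loss may never be triggered.

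**Working it through.** **1. The plan's own sample size.** Inputs from Sample Size and Power: d = 0.2, 80% power, alpha 0.05/3 = 0.0167, taken as two-sided (not stated, but it reproduces the figure).

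n per arm = 2(z₁₋α/₂ + z₁₋β)²/d² = 2(2.394 + 0.842)²/0.04 ≈ 524, as stated.

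524/0.70 = 748.6, against the stated 748 (749 if rounded up).

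**2. Who contributes.** For one end point, a participant's likelihood term is f(30-day score | arm, baseline covariates, block effect). If that score is missing, integrating over it gives 1. The term vanishes and the fit is the complete-case fit. Two numerical checks on simulated data agree:

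- Regression on arm and baseline, without block, 1032 of 1496 outcomes observed: EM over the missing outcomes and the complete-case fit both gave a treatment coefficient of -0.23503557.
- Block random-intercept model, fitted with and without the rows lacking an outcome: 1051 participants used both times, with identical coefficient and SE.

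The equivalence with multiple imputation does not help, because imputing from the same regression adds no information about these participants.

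**3. The joint model.** It keeps a participant with one or two of the three end points observed. It cannot keep one who missed the whole survey, which is the pattern the plan expects for most missing data.

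**4. Size.** At 30% attrition:

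- analysed: 0.70 × 1496 ≈ 1047 (523.6 per arm)
- not contributing: 0.30 × 1496 ≈ 449

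Actual retention is not given. At 20% attrition 80% would be analysed; at 40%, 60%.

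**5. Power.** Power = Φ(d√(n/2) − z₁₋α/₂):

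- n = 523.6 per arm: Φ(3.236 − 2.394) = 80.0%
- n = 748 per arm: Φ(3.868 − 2.394) = 93.0%

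The planned 80% already assumes that only about 524 per arm supply outcomes. The sample size section thus budgets for the loss that the missing-data text says is avoided.

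**6. Bias, by illustration only.** The parameters here are assumptions, not taken from the protocol: 748 per arm, 30% loss, true effect -0.20 SD, correlations of 0.6 to 0.7 between baseline, 2-week and 30-day scores, and dropout log-odds of 0.5, 1.0 or 1.5 per SD of the 2-week state. In controls that state exists but is not measured. Ranges cover repeat runs.

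| Dropout depends on 2-week state | Mean estimate, planned model (true -0.20) |
|---|---|
| Not at all | -0.20 |
| Intervention arm only, 0.5 / 1.0 / 1.5 | -0.24 to -0.25 / -0.28 to -0.29 / -0.30 to -0.31 |
| Both arms, same slope, 0.5 / 1.0 / 1.5 | about -0.20 in each |

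A separate simulation with dropout depending on baseline only gave -0.201. The direction and size of any bias therefore turn on whether the dependence differs between arms, and the protocol gives no data on that.

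**7. Would imputing from the 2-week scores help?** In the equal-slope scenarios, imputing by arm with the 2-week score in the intervention arm and baseline only in controls moved the estimate to about -0.15, -0.11 to -0.12, and -0.08 to -0.09 against -0.20. It corrects one arm and leaves the other.

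**The case against.** The strongest reply is that complete-case regression adjusted for baseline, with one follow-up, is a standard analysis and valid under missing at random given arm, block and the model's covariates. That stands. The objection here is to the property claimed for the model and to the breadth of the stated assumption, not to the choice of estimator.

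The claim is also partly true: the joint model does retain people with some end points observed. That stands too, but it does not reach unit nonresponse.

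Three stronger readings are tempting, and the document supports none of them.

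- **The primary effect will be exaggerated.** This needs intervention-arm dropout to follow post-baseline symptoms while control-arm dropout does not. Both arms answer in the app, with the same 30-day notification and reminder emails. Only the intervention arm has the full app, feature notifications and Peer Coach contact, so a difference is conceivable, but nothing in the protocol establishes it. The steepest slope used above (1.5, an odds ratio of about 4.5 per SD) has no source in the document.
- **The trial is underpowered.** It is not on this account: the inflation to 748 already covers the loss.
- **The intention-to-treat label is false.** The protocol uses the term for analysis as assigned regardless of app use, and that is preserved. What fails is the statement that participants without an outcome contribute.

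A sensitivity method for nonrandom missingness is already named, and its detail may properly sit in an analysis plan. What remains is the trigger: whether data are missing not at random after conditioning on what is observed cannot be settled from those data, so a check made conditional on suspicion has no workable criterion.

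**Conclusion.** The statement is wrong as written for the kind of missingness that the plan itself expects. Participants with no 30-day survey do not enter the treatment estimate: about 449 of 1496 at the assumed 30% attrition, leaving a complete-case analysis of about 524 per arm. The joint test additionally keeps those with at least one of the three end points. Validity requires that nonresponse depend on no more than arm, block and the included baseline covariates. Whether the estimate is biased cannot be determined from the protocol. The conclusion rests on the model as specified; it would change if baseline or interim scores were modelled as responses, which the protocol does not say.

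**What to change.** 1. Delete the claims that the models include participants with missing outcomes and that they avoid loss of power.
2. State that the primary analysis uses participants with an observed 30-day outcome (at least one of the three for the joint test), valid under missing at random given arm, block and the listed baseline covariates.
3. Include baseline variables that predict nonresponse, for example the baseline values of all three primary outcomes and the randomization stratum. The present rule picks candidate covariates by between-arm imbalance (Cohen d above 0.05), which does not ensure this.
4. Run the isni analysis unconditionally, and add a delta (tipping-point) analysis in which the shift for nonresponders varies separately by arm.
5. Do not put the intervention-only 2-week scores or app use into the primary imputation. Use them at most in a sensitivity analysis labelled as correcting one arm only, and run so that the statistician stays blinded.

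The cost is wording and some programming. No new data or change in sample size is needed.

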#### Masking

The study will use a single-blinded approach where only the investigators (including the statistician) will be blinded to the treatment group assignment when examining the primary hypotheses.

### Continued Monitoring

There will be no stopping rules in this study—the anticipated benefits and unanticipated adverse effects are not life threatening and too small to merit such an approach. In addition, there will be no sequential analyses of the data: the analyses will commence at the end of the trial when the data manager provides the statistician with a blinded database for the analyses. Of note, data from the 2-week assessment completed by the intervention group will be removed from the data set used for the primary outcome analysis to maintain the blinding of the statistician.

### Ethics Approval

This study was approved by the UBC Behavioral Research Ethics Board on January 6, 2022 (ethics ID: H21-03248). Any changes to the protocol will be submitted for approval to the UBC Research Ethics Board.

### Consent

Consent will be obtained using a web-based UBC Qualtrics form before the email validation process (ensuring current student enrollment and only 1 study registration per student), which provides access to the app and baseline assessment survey.

## Results

The trial was registered on ClinicalTrials.gov (NCT05606601) on November 4, 2022. Recruitment and data collection began in September 2022. As of May 10, 2022, a total of 1425 participants have been enrolled. The results of the study will be available at the end of 2023 and will be published in international and national journals and presented at conferences.

## Discussion

### Expected Findings

Postsecondary students have been found to have high rates of mental health and substance use problems but many of these students do not access mental health or other professional supports [10]. e-Interventions have been shown to be effective among university students and may help address barriers to seeking support by providing tools that are easily accessible and can be scaled up for university campuses [16]. This manuscript describes the study protocol for a RCT to assess whether the *Minder* app is effective in improving mental health and substance use outcomes in a general population of Canadian university students. We hypothesize that individuals assigned to the intervention group will be more likely to experience improvements in mental health and substance use outcomes compared with individuals in the control condition. Additional secondary outcomes and analyses seek to inform potential mechanisms through which future studies can be conducted to better understand how to support the mental well-being of students and support the ongoing improvement of the *Minder* app as an effective digital mental health tool.

### Limitations

Although many similar e-interventions have experienced large loss to follow-up and poor participant engagement, the incorporation of Peer Coaches for each participant in addition to well-spaced reminders to return to the app and complete baseline and follow-up surveys are expected to improve app engagement and reduce loss to follow-up. It is also important to note that this intervention was designed for use in the general population with mild symptomology so recruitment may be challenging as these students may be less interested than a clinical population in participating in a mental health study. We have addressed this challenge by using a comprehensive set of recruitment methods to engage potential participants in the broader university population. The intervention also includes components relevant to all students, including content addressing general well-being and more clinically relevant content. Students who choose to participate in this study may also be more motivated than the general population to seek help or to improve their mental health or substance use concerns. This may impact their willingness to participate and responses to self-report surveys, which may lead to reporting bias; however, we believe that these biases will not differ across the surveys or between intervention and control groups. Moreover, mental health and substance use concerns are high among university populations, with a large fraction experiencing psychological distress; therefore, a study sample reporting a range—including elevated levels—of mental health or substance use concerns is representative of students’ functioning, which supports the generalizability of the results to the broader student population. In addition, participants in the intervention group will be unblinded, which could lead to biased self-reports of mental health symptomology related to placebo effects and social desirability. Although our use of standardized assessments completed via nonidentifiable web-based surveys should help mitigate some of these risks, it will be important to address this limitation in future studies on the *Minder* app by incorporating a sham or placebo control in future trials and examining the cognitive mechanisms associated with targeted outcomes.

### Conclusions

Despite these limitations, the findings from this trial will inform the ongoing refinement of the *Minder* app. One key aspect of the *Minder* app that separates it from other similar tools is its extensive codevelopment process with students, especially in the development of content that is presented in a chatbot manner that is more interactive than other modular, web-based CBT interventions. It is designed to support a general population of students across many potential topics, whereas many existing tools target specific issues (eg, depression or anxiety). Thus, by designing a tool that can be used by all students, we hope to provide a suite of interventions (eg, from time management to managing emotions) that builds resilience across a range of conditions and improves the well-being of students as they face the many challenges associated with postsecondary education and young adulthood. This includes the tailoring and ongoing improvement of content using focus groups and continued engagement with specific groups of university students who may have more unique university experiences, including international students; lesbian, gay, bisexual, transgender, queer, 2-spirit, intersex, asexual, and similar minority (LGBTQ2IA+) students; and Indigenous and other racialized students. Through further analyses of app use data and subgroup analyses, we hope to identify areas of particular interest and need to help us better understand how to improve and scale up the delivery of the app to other student populations.

## Appendix

Multimedia Appendix 1 Secondary outcome questions.

## Abbreviations

AUDIT: Alcohol Use Disorders Identification Test
CACE: Complier Average Causal Effect
CBT: cognitive behavioral therapy
GAD-7: General Anxiety Disorder 7-Item
GLMM: generalized linear mixed-effect model
ITT: intention to treat
LGBTQ2IA+: lesbian, gay, bisexual, transgender, queer, 2-spirit, intersex, asexual, and similar minority
PHQ-9: Patient Health Questionnaire 9-Item
RCT: randomized controlled trial
SAC: Student Advisory Committee
UBC: University of British Columbia
USAUDIT-C: US Alcohol Use Disorders Identification Test-Consumption Scale
